  - Visual Analogue Scale (10 cm): evaluation for dyspnea, thoracic and abdominal rest and incident pain
  - Airway secretion score: ask patient to cough and subjectively evaluate presence and consistency of sputum; if yes: purulent *or* not
  - Chest X-ray – not mandatory
  - Noninvasive mean arterial pressure; mmHg
  - Heart rate; BPM

- Body temperature; °C
- BUN, Creatinine, AST, ALT, Bilirubin, Hb, Platelets, PT, PTT, WBC count

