### *Post-operative variables*

The patients will be assessed daily between the first and the fifth day after surgery as well as on the last day before discharge from hospital. Clinical data and the presence of pulmonary and extra-pulmonary postoperative complications will be scored, the date of development of any complication documented (for definitions, see APPENDIX iii.).

The documentation will adhere to the timetable in APPENDIX iv.

- Continuation of non-invasive or invasive mechanical ventilation outside of the operation room directly after surgery; if yes: specify indication and duration, hours
- Any new requirement of non-invasive CPAP or NPPV; if yes: specify indication, duration and intensity
- Any new requirement of invasive mechanical ventilation; if yes: specify indication, duration and intensity
- ICU stay directly postoperative; if yes: specify reason

- Any new admission or readmission to the ICU at any time in the post–operative period; if yes: specify reason
- Postoperative nausea and vomiting (PONV)
- Physiotherapy and breathing exercises
- CAS  to evaluate mobility, see Appendix ii
- Wound healing: impaired wound healing can be defined as an interruption in the timely and predictable recovery of mechanical integrity in the injured tissue
- Surgical wound infection; if yes: specify location (superficial *or* deep, abscess, empyema *or* phlegmon )
- Return of bowel function
- Any need for anti–arrhythmic and vasoactive medication; if yes: specify
- Post–operative fluid requirements (crystalloids, artificial colloids, or albumin; specify type and amount since last assessment)
- Post–operative transfusion of packed red blood cells, fresh frozen plasma , plasma frozen within 24 hours (FP24), fibrinogen, cryoprecipitate, PPSB and platelets in the preceding six hours; if yes: specify type and number of units transfused since last assessment
- Respiratory rate and peripheral oxygen saturation in room air, beach chair position
- Presence or absence of airway secretion (ask patient to cough and subjectively evaluate presence and consistency of sputum; if yes: purulent *or* not)
- Noninvasive mean arterial pressure
- Heart rate (bpm)
- Tympanic temperature; °C
- VAS evaluation for dyspnea, thoracic and abdominal rest and incident pain
- Chest X–ray – not mandatory
- Bedside spirometry (FVC, FEV1) – not mandatory
- BUN, Creatinine, AST, ALT, Bilirubin, Hb, Platelets, PT, PTT, white blood cell count

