### 7.2.5 Blood and urine samples

Before, at the end of, and five days after surgery, blood samples (2 x 5 ml in EDTA, citrate and heparin) and urine samples will be collected and stored at –80°C for measurement of:

- Inflammatory mediators (cytokines, chemokines, other inflammatory proteins)
- Markers of lung injury (angiopoietin-2, surfactant proteins A and D)
- Specific markers of distal organ injury (e.g., cystatin C, NGAL)

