With regard to the remaining parameters: Normally distributed variables will be expressed by their mean and standard deviation; non-normally distributed variables will be expressed by their medians and interquartile ranges. Categorical variables will be expressed as n (%). Student's *t*-test will be used to test groups of continuous normally distributed variables. Conversely, if continuous data is non-normally distributed, the Mann-Whitney-*U* test will be used. Categorical variables will be compared with the Chi-square test, Fisher's exact tests or, where appropriate, as relative risks. Time dependent data will be analyzed using a proportional hazard model adjusted for possible imbalances of patients' baseline characteristics.

Data analyses will follow an a priori documented statistical analysis plan which will be finalized before the end of data collection. By definition, only the analysis of the primary outcome is confirmatory, all other analyses are exploratory. The analysis strategy follows the intention-to-treat principle. The analysis will be undertaken blinded by a statistical expert. Statistical significance is considered to be at a *p*-value of 0.05. Where appropriate, statistical uncertainty will be expressed by 95% confidence levels.

The analysis will be performed with SPSS.

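### Section 8.2 gives the biomarkers and other continuous variables an unadjusted two-sample test although a pre-operative value is collected: valid, but less precise than baseline adjustment

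*Protocol*

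**What the plan says.** Section 8.2 of the protocol introduces one rule with the words "With regard to the remaining parameters". Student's t-test "will be used to test groups of continuous normally distributed variables". The alternative follows at once: "Conversely, if continuous data is non-normally distributed, the Mann-Whitney" U test applies. No covariate, analysis of covariance or repeated-measures model is named for continuous data. The only baseline adjustment in that paragraph is for time-dependent data, which get a "proportional hazard model adjusted for possible imbalances of patients' baseline characteristics".

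The data collection sections show which continuous variables have a baseline:

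- **Biomarkers** of inflammation, lung injury and distal organ injury are the parameters listed in Section 7.1.3. Section 7.2.5 schedules them at three times: "Before, at the end of, and five days after surgery, blood samples" and urine samples are taken.
- **Symptom scores** are recorded among the pre-operative variables of Section 7.2.4 ("Visual Analogue Scale (10 cm): evaluation for dyspnea, thoracic and abdominal rest and incident pain") and again after surgery.
- **Room-air SpO2** is recorded before surgery and at the post-operative visits ("Respiratory rate and peripheral oxygen saturation in room air, beach chair position").
- **Spirometry, routine laboratory values and the Cumulated Ambulation Score** appear in both the pre-operative and the post-operative lists. Appendix iv marks spirometry, laboratory tests and special-marker sampling as optional.

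Section 8.2 also limits the weight of these analyses: "By definition, only the analysis of the primary outcome is confirmatory, all other analyses are exploratory". It refers to a separate SAP, which was not available for this review.

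**The concern.** When the same quantity is measured before randomized treatment and after it, part of the spread in the later value is stable difference between patients. A two-sample test of the later value leaves that part in the error term. Using the pre-operative value as a covariate removes it.

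The stake is the width of the confidence intervals for the mechanistic comparisons. It is largest for the biomarkers: they are listed parameters, they require extra blood from patients, and because sampling is optional they will probably exist in only part of the trial population.

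This goes beyond detail left to the SAP. The protocol names a specific test for these variables and reserves baseline adjustment for a model suited to times to event, not to marker levels or saturation readings.

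**Working it through.** **The plan's own figures.** Section 8.2 and Section 6.4 give no figure for any continuous outcome. The sample size concerns the binary primary endpoint only. It reproduces: 906 per group in a fixed design for 0.20 versus 0.15; power of 0.803 to 0.805 at N = 1912 with the stated boundaries; 1912 / 0.95 = 2013 with dropout. Nothing below alters it.

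**Inputs.** The correlation rho between the pre-operative and the post-operative value is not in the protocol. It is assumed to be 0.3, 0.5 or 0.7. Allocation is 1:1. The change-score formula also assumes equal variance before and after surgery.

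**Formulas**, each relative to a t-test of the post-operative value alone:

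- ANCOVA variance factor: 1 - rho^2
- Confidence interval width factor: sqrt(1 - rho^2)
- Extra patients the unadjusted test needs for equal precision: 1/(1 - rho^2) - 1
- Power of ANCOVA where the unadjusted test has 80%: Phi((1.960 + 0.842)/sqrt(1 - rho^2) - 1.960)
- Change-score variance factor: 2(1 - rho)

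| Assumed rho | ANCOVA variance | CI width | Extra patients for unadjusted test | ANCOVA power | Change-score variance |
|---|---|---|---|---|---|
| 0.3 | 1 - 0.09 = 0.91 | 0.954 | 10% | 83.6% | 2 x 0.7 = 1.4 |
| 0.5 | 1 - 0.25 = 0.75 | 0.866 | 33% | 89.9% | 2 x 0.5 = 1.0 |
| 0.7 | 1 - 0.49 = 0.51 | 0.714 | 96% | 97.5% | 2 x 0.3 = 0.6 |

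**Both readings of the rule.** Section 8.2 does not say whether the test applies to the post-operative value or to the change from baseline. The difference between the change-score and ANCOVA factors is 2(1 - rho) - (1 - rho^2) = (1 - rho)^2, which is never negative. So ANCOVA is at least as precise under either reading, and below rho = 0.5 a change score is less precise than ignoring the baseline.

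**Which variables are affected.** The primary endpoint is binary. Among the secondary endpoints of Section 7.1.2 the one clearly continuous item is hospital-free days, which has no baseline. That leaves the biomarkers of Section 7.1.3 and variables that are collected but not listed as endpoints.

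**The case against.** The case against has four parts.

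*Nothing confirmatory depends on it.* This stands. Section 8.2 makes every non-primary analysis exploratory, and apart from the biomarkers the variables concerned are collected data, not endpoints. It lowers the priority. It does not make the less precise test the better choice.

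*Validity.* A reader might infer that an unadjusted test biases the comparison, because a chance baseline difference carries into the result. The protocol does not support that. Randomization keeps the unadjusted comparison valid, and its standard error already allows for chance imbalance. The loss is precision only.

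*Wording.* A reader might also infer that Section 8.2 prescribes raw post-operative values and throws the baseline away. The text does not say so; a t-test on changes would fit the sentence and would use the baseline. The criticism holds under both readings, but for different reasons, as the two variance factors show.

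*The size is assumed, and one linear model does not suit everything.* Both parts stand. With no rho in the protocol the gain runs from small to large, and at 0.3 the interval narrows by only about 5%. The factor 1 - rho^2 is for linear adjustment of a mean. It does not carry over directly to the Mann-Whitney branch, to bounded scales, or to the ambulation score, an ordinal sum of three items scored 0 to 2 (range 0 to 6). Nor is there a single post-operative value for variables recorded on days 1 to 5.

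The SAP might already adjust for baseline. If so, Section 8.2 should be aligned with it, because as written it names a different method.

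**Conclusion.** The point holds as a matter of precision. Section 8.2 names unadjusted tests for continuous variables whose pre-operative value the trial already collects. Against a test of the post-operative value, adjustment would cut the variance by 9%, 25% or 51% at an assumed rho of 0.3, 0.5 or 0.7; against a change score it is never worse. These factors describe large samples and linear adjustment on a suitable scale.

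The unadjusted tests are not wrong. The primary endpoint, the listed secondary endpoints and the sample size of 1912 (2013 with dropout) are untouched. The improvement matters most for the optional biomarkers and is worth making because it needs no new data.

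**What to change.** Amend the rule in Section 8.2, or state the method in the SAP before it is finalized and align Section 8.2 with it:

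1. **Biomarkers:** at each post-operative time point (end of surgery, day 5), use ANCOVA of the log value on treatment with the log pre-operative value as covariate. Report the adjusted ratio with its 95% confidence interval.
2. **Other continuous variables with a pre-operative value**, if compared between arms: use a repeated-measures model with baseline as covariate for the daily day 1 to 5 measurements.
3. **Ambulation score:** use an ordinal model with the baseline score as covariate.
4. **Missing optional baseline:** keep the patient by mean imputation of the baseline or a missing indicator.
5. **Variables without a baseline**, such as hospital-free days and blood loss: keep the two-sample tests.

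The cost is a few sentences and slightly more analysis work. No visit, sample or patient is added.

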#### 6.4 Sample size calculation

**Initial** sample size calculation was based on our primary hypothesis and primary study outcome, and was informed by data collected during a multicenter Spanish trial (ARISCAT) (see APPENDIX i) and a single-center, relatively small study reporting the effects of intraoperative higher PEEP and recruitment maneuvers on the incidence of postoperative desaturation, chest infection and bronchospasm in obese patients who underwent laparoscopic bariatric surgery.

These calculations indicated that 356 patients were required per group, assuming a two-sided significance level of 0.05 and a power of 80%, to detect the expected difference in postoperative pulmonary complications between the higher PEEP group of 30% and the lower PEEP group of 40% (risk ratio of 0.75). Assuming a dropout rate of 5%, **a total of 748 patients** (n=374 per group) were planned to be included into the study.

Sample size was re-estimated based on recommendations of the DSMB after data on the first 618 patients revealed that the incidence of the collapsed composite outcome was considerably lower than expected. In the revised calculations, the control group incidence was assumed to be 0.20 (instead of 0.40), and sample size was calculated to have 80% power at the overall 0.05 significance level to detect a relative risk (as originally planned) of 0.75. This design requires a maximum of 1912 patients, adjusting for the interim monitoring for efficacy and futility as described in section 8.2. Assuming a dropout rate of 5%, a total of 2013 patients need to be included into the study. East 6.0 interim monitoring software (Cytel, Cambridge, MA, USA) was used.

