### 8.2 Analysis

The primary endpoint is a collapsed composite of postoperative pulmonary complications occurring in the first five days after surgery. These complications include aspiration pneumonitis, bronchospasm, mild respiratory failure, moderate respiratory failure, severe respiratory failure, development of acute respiratory distress syndrome, pulmonary infection, atelectasis, pulmonary edema caused by cardiac failure, pleural effusion, pneumothorax and new pulmonary infiltrates (for definition, see Appendix iii). Patients who develop a least one of the above mentioned complications are considered as meeting the primary endpoint.

Interim analyses for efficacy and futility will be conducted at 50% (N=956), 75% (N=1434) and 100% (N=1912) of the planned enrollment, as needed, using a non-binding group sequential design with gamma spending functions ( $\gamma = -4$  for each of  $\alpha$  and  $\beta$ ). The table below shows the  $\alpha$  and  $\beta$  spent over the trial, z-statistic boundaries for efficacy and futility, and boundary crossing probabilities under the alternative hypothesis ( $H_1$ ). The corresponding P-value boundaries for efficacy (futility in parentheses) at the 1st, 2nd and final looks, respectively, are  $P \leq 0.006$  ( $P > 0.82$ ),  $P \leq 0.015$  ( $P > 0.35$ ) and  $P \leq 0.044$  ( $P > 0.044$ ). The Figure below displays the z-statistic boundaries for efficacy/harm and futility as a function of accrued sample size.

| Table: Z-statistic boundaries and boundary crossing probabilities (under $H_1$ );
Power=0.80, $\alpha=0.05$ , gamma spending functions ( $\gamma = -4$ ), $p_1=.20$ , $p_2=0.15$ |                      |      |                        |                 |              |             |                                             |          |
|-------------------------------------------------------------------------------------------------------------------------------------------------------------------------------------|----------------------|------|------------------------|-----------------|--------------|-------------|---------------------------------------------|----------|

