| Look                                                                                                                                                                                | Information Fraction | N    | Cumulative Alpha spent | Cum. Beta spent | Z- efficacy  | Z- futility | Boundary crossing probabilities under $H_1$ |          |
|                                                                                                                                                                                     |                      |      |                        |                 |              |             | Efficacy                                    | Futility |
| 1                                                                                                                                                                                   | 0.5                  | 956  | 0.006                  | 0.024           | $\geq 2.75$  | $< 0.225$   | 0.234                                       | 0.024    |
| 2                                                                                                                                                                                   | 0.75                 | 1434 | 0.018                  | 0.071           | $\geq 2.432$ | $< 0.929$   | 0.296                                       | 0.047    |
| 3                                                                                                                                                                                   | 1                    | 1912 | 0.05                   | 0.2             | $\geq 2.012$ | $< 2.012$   | 0.271                                       | 0.129    |

[figure not shown]

For the primary efficacy analysis rates of postoperative pulmonary complications will be compared between the two intervention groups and the odds ratio relative risks with corresponding 95% confidence levels interval will be calculated using logistic regression analysis.

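### Section 8.2 sets significance at p = 0.05 without qualification, which conflicts with its own final-look boundary of P ≤ 0.044 for the primary outcome

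*Protocol*

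**What the plan says.** Section 6.4 gives the design target: "sample size was calculated to have 80% power at the overall 0.05 significance level to detect a relative risk (as originally planned) of 0.75". Here 0.05 is explicitly an overall level.

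Section 8.2 then sets out the monitoring: "Interim analyses for efficacy and futility will be conducted at 50% (N=956), 75% (N=1434) and 100% (N=1912) of the planned enrollment, as needed". Alpha and beta are each spent by a gamma function with γ = −4, and the futility boundary is non-binding. The section lists "P-value boundaries for efficacy (futility in parentheses) at the 1st, 2nd and final looks": P ≤ 0.006, P ≤ 0.015 and P ≤ 0.044. The table gives the same rule as Z ≥ 2.75, 2.432 and 2.012, with cumulative alpha 0.006, 0.018 and 0.05. After the table, the primary efficacy analysis is described as a logistic regression reported with a 95% interval.

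The last paragraphs of Section 8.2 first deal with the remaining parameters. A general paragraph follows. It says that only the primary outcome analysis is confirmatory, that the analysis is by intention to treat, and that it is done blinded. It then adds "Statistical significance is considered to be at a *p*-value of 0.05". The same paragraph requires a "statistical analysis plan which will be finalized before the end of data collection".

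**The concern.** The trial has one confirmatory test, and Section 8.2 gives two thresholds that can be read as applying to it. The 0.05 sentence is not in the paragraph on the remaining parameters. It is in the general paragraph that names the primary outcome as the confirmatory one, and it says neither that 0.05 is the overall level nor that it is meant for exploratory outcomes.

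A final P between 0.044 and 0.05 would then be a success under one sentence and a failure under another. The ordinary 95% interval for the primary effect has the same gap, because in that range it excludes no effect while the efficacy boundary is not crossed.

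A flat 0.05 would suit a design without interim looks, which is what the change list for version 2.4.2 describes. The sentence may have been left in place when version 2.5 added the looks. That is an inference; the conflict stands on the current text alone.

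**Working it through.** **Inputs.** Overall α = 0.05 (Section 6.4). Information fractions t = 0.5, 0.75 and 1, gamma spending with γ = −4, and non-binding futility at Z < 0.225 and Z < 0.929 for the first two looks (Section 8.2). The test is taken as two-sided, because the stated P boundaries equal 2(1 − Φ(z)) and the figure is described as showing efficacy/harm boundaries.

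**Step 1: reproduce the plan's boundaries.** The spending function is α(t) = 0.05 × (1 − e^(4t)) / (1 − e^4).

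- t = 0.5: 0.05 × 6.389 / 53.598 = 0.00596 (stated 0.006)
- t = 0.75: 0.05 × 19.086 / 53.598 = 0.01780 (stated 0.018)
- t = 1: 0.05 (stated 0.05)

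The boundaries are solved from the joint normal distribution of Z₁, Z₂, Z₃ with corr(Zᵢ, Zⱼ) = √(tᵢ/tⱼ) for tᵢ < tⱼ. The correlations are 0.816 (looks 1 and 2), 0.866 (looks 2 and 3) and 0.707 (looks 1 and 3).

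| Look | Derived Z | Stated Z | Derived two-sided P | Stated P |
|---|---|---|---|---|
| 1 | 2.750 | 2.75 | 0.0060 | 0.006 |
| 2 | 2.432 | 2.432 | 0.0150 | 0.015 |
| 3 | 2.011 | 2.012 | 0.0443 | 0.044 |

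The futility values also reproduce: Z = 0.225 gives P = 0.822 and Z = 0.929 gives P = 0.353 (stated 0.82 and 0.35). The table is sound.

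**Step 2: type I error with each final threshold.** With c the final critical value and futility ignored, as a non-binding design requires:

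α = 1 − Pr(|Z₁| < 2.75, |Z₂| < 2.432, |Z₃| < c) under no effect.

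| Final threshold | Futility non-binding | Futility stops always obeyed |
|---|---|---|
| c = 2.012 (P ≤ 0.044) | 0.050 | 0.048 |
| c = 1.960 (P ≤ 0.05) | 0.055 | 0.053 |

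Recursive integration and the multivariate normal distribution function agree for the non-binding column (0.0551 and 0.0552 for c = 1.960).

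**Step 3: dependence on the looks taken.** The plan says the looks are held as needed. With only one interim look at its listed boundary and 0.05 at the end, the error is 0.0524 (50% look) or 0.0534 (75% look). With no interim look, 0.05 at the end is valid.

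**Step 4: interval.** Z = 2.012 corresponds to P = 2(1 − Φ(2.012)) = 0.0442. The matching coverage is 1 − 0.0442 = 0.9558, or about 95.6%. If test and interval come from the same model statistic, a 95% interval excludes no effect whenever P < 0.05. The two therefore disagree for P between 0.044 and 0.05.

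**Step 5: cost in power.** With 956 patients per arm, event rates 0.20 and 0.15, the stated boundaries and futility stops obeyed, power is 0.803 (pooled variance) to 0.805 (unpooled). The 1,912 patients therefore already allow for the final boundary of 2.012.

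**The case against.** The strongest reply is that the specific rule governs. Section 8.2 prints a P boundary for every look, repeats it on the Z scale, and gives the final futility side as P > 0.044, so a final P of 0.047 is already classified as not crossing. The 0.05 sentence can be read as the overall level, in line with Section 6.4 and the table's cumulative alpha, or as the level for exploratory outcomes. This largely stands, and it is why the point is minor. It does not remove the point, because the sentence states neither reading and a confirmatory criterion should not need interpretation.

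It can also be said that the interval expresses uncertainty and is not the decision rule, and that ordinary 95% intervals are common beside sequential decisions. That is fair, and labelling the interval as unadjusted would be enough.

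Three stronger readings are tempting but not supported:

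- **A reader might infer that 0.05 applies at every look.** The boundary printed for each look rules this out.
- **A reader might infer that the SAP is to be written after the unblinded looks, leaving the confirmatory analysis open to choice.** The sentence sets only a latest date. Section 8.3 gives interim results to the DSMB, and Section 8.2 has the analysis done blinded. The primary endpoint, the regression method and the boundaries are already fixed there. What remains is that the deadline permits, without requiring, finalisation after comparative results exist.
- **A reader might infer that 0.05 belongs to the exploratory analyses alone.** That would clash with Section 6.4, where 0.05 is the overall level of the primary test.

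**Conclusion.** The conflict is real and confined to one sentence and the unadjusted interval; the group sequential design itself controls the error at 0.05. Applying 0.05 to the primary outcome at the final look, after both interim looks at their listed boundaries, would raise the overall two-sided type I error by about half a percentage point, to 0.055 (0.053 if futility stops are always obeyed). The figure of 0.055 assumes looks at exactly 50%, 75% and 100% of information and futility treated as non-binding, as the protocol says. The excess is smaller with one interim look and absent with none. In practice the two thresholds lead to different conclusions only for a final P between 0.044 and 0.05. This is a minor correction, worth making because it concerns the threshold of the only confirmatory test.

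**What to change.** Replace the significance sentence in Section 8.2 with text to this effect: *For the primary outcome, 0.05 is the overall two-sided significance level. The outcome is significant only if the efficacy boundary for that look is crossed (P ≤ 0.006, 0.015 and 0.044 at the first, second and final looks). Its confidence interval is reported at the matching level (about 95.6% at the final look) or is labelled as unadjusted for the interim looks. An unadjusted 0.05 level and 95% intervals apply to the exploratory analyses.* Align the 95% interval named in the primary efficacy analysis with this wording.

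As a secondary safeguard, require the SAP to be final before the first interim efficacy analysis.

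The cost is a few sentences and an earlier SAP deadline. Sample size and planned power do not change, because the 1,912 patients already assume the final boundary of 2.012.
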